### Sample size

The recruitment target is thirty-four wards. Based on a recent survey of acute inpatient wards across the NHS, it is estimated that there will be an average of 24 beds per ward (range 18-30) giving a pool of 816 patients at baseline across 34 wards. Based on the same survey, it is estimated that there will be an average of 25 staff per ward giving a potential pool of 850 staff across 34 wards. Based on trials of psychological therapy in inpatient settings [27, 30] it has been conservatively estimated that recruitment rates for the completion of individual level outcome measures at baseline will be 80% of eligible staff and 50% of eligible patients giving a pool of 680 staff and 408 patients.

For the primary outcome of number of serious incidents on the ward, assuming 5.22 mean number of events in the control arm [31], 16 wards per arm has more than 80% power to detect a reduction in mean number of events to 3.13 (40% relative reduction), assuming a poisson distribution for the outcome. To allow for possible dropout of a ward, we will recruit 34 wards in total.

For the individual level health related primary outcome (WEBWBS) and other individual level secondary outcomes, we used the –clustersampsi- command in Stata. We assume a between group effect size of 0.4 and an intra-cluster correlation coefficient of 0.05. We allow for a baseline-endpoint correlation of 0.3, which we suggest is conservatively low given the short time span between baseline and endpoint. We specified 85% power, 5% significance level, and calculated the average cluster size (i.e. how many participants were required to be recruited in each cluster). The optimal design for these parameters requires 9 participants per cluster. This leads to a total sample size per arm of 153, and 306 for the analysis set. Accounting for attrition of 20%, by making an adjustment to this value, 383 participants are required at baseline. This assumes that attrition is consistent across treatment arms and clusters. Therefore the aim is to recruit 34 clusters with 11 participants in each cluster, giving a total sample size at baseline of 384. Adjustments will be made for additional covariates in order to preserve 85% power against a larger observed ICC value or a weaker observed baseline-endpoint correlation.

We assume a between group effect size of 0.4 for individual level health primary outcome measure (WEMWBS) and also secondary outcome measures for two reasons. First, meta-analytic reviews show that the overall effect size Cognitive Behaviour Therapy for psychosis trials is 0.4 (e.g. [13]). Second, the population norms for the WEMWBS gives a SD of 8.7, so the effect size corresponds to a between-group difference of 3.5 on the scale. According to the WEMWBS user guide (2015) investigations suggest that a change of three or more points is likely to be recognisable to an individual and different statistical methods provide estimates ranging from three points to eight points. The guide also cites a study which corroborates the importance of a change of three or more points on the WEMWBS by demonstrating correlations between score changes on WEMWBS and clinical assessment of change in the context of a counselling service; an effect only evident at three points and above. Below a three-point change, the extent of change in WEMWBS was not correlated with change assessed as clinically significant (see https://warwick.ac.uk/fac/sci/med/research/platform/wemwbs/development/papers/margerita_aucc_analysis_3.pdf).

At the 6-month follow-up where additional patients will be recruited to complete the VOICE they will also complete the primary outcome measure (WEMWBS). This is to ensure the primary outcome measure is sufficiently powered. 9 patients per cluster will be recruited, as per the aforementioned optimal design for the defined power and significance level parameters, as these participants will not receive a follow-up, we do not need to take into account drop-out rates.

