### Data analysis

Analysis will follow intention-to-treat principles: outcome data will be sought and included in the analysis for all patients irrespective of receipt of the intervention during the time scale of the trial. The CONSORT statement for cluster RCT's will be followed. Treatment effects for the cluster (ward) level outcomes will be estimated using appropriate mixed models with a fixed effect for ward gender, and a random intercept for the ward.

Individual (patient/staff) level outcomes measures will be analysed using an appropriate generalised linear mixed model with random intercepts for wards. With the exception of patient ward atmosphere (VOICE), the baseline values of the outcomes can be used as a covariate in the models.

A statistical analysis plan for primary and secondary outcomes, including sub-group analyses will be presented to and agreed with the programme steering group prior to the allocation codes being revealed and commencement of any data analysis. There are no planned interim analyses.

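### The stated power above 80% for serious incidents holds only if all wards share essentially the same underlying incident rate, an assumption at odds with the protocol's own analysis model

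*Protocol article*

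**What the plan says.** The Sample size section of the protocol article powers the ward-level co-primary outcome in one sentence. It starts from "assuming 5.22 mean number of events in the control arm" and claims that "16 wards per arm has more than 80% power to detect a reduction in mean number of events to 3.13 (40% relative reduction"). The distributional basis offered for this claim is "assuming a poisson distribution for the outcome". The section then adds: "To allow for possible dropout of a ward, we will recruit 34 wards in total". That makes 17 wards per arm, or 16 after one dropout in each. The sentence gives no between-ward CV, dispersion parameter or ICC for incidents, no significance level, and no time window for the 5.22.

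Elsewhere the article treats wards as different from one another:

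- The Sample size section reports "an average of 24 beds per ward (range 18-30") and allows an ICC of 0.05 for WEMWBS.
- The Outcome measures section defines the outcome as the total number of incidents per ward, with no per-bed offset mentioned. Counts cover the preceding 3 months, at baseline and at 3, 6 and 9 months.
- The Data analysis section will use "appropriate mixed models with a fixed effect for ward gender, and a random intercept for the ward" for ward-level outcomes.

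**The concern.** A Poisson count has variance equal to its mean. Applied to ward totals within an arm, this means every ward has the same underlying rate and differs from the others only by chance. A ward random intercept is fitted because that is not expected to be true. The power calculation therefore sets to zero a variance that the analysis model will estimate. Ward size feeds directly into a total count, and Trust, case mix and reporting practice are further possible sources of spread.

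The calculation supports the number of wards: 16 per arm, raised to 34 in total, and the WEMWBS design uses the same 34 clusters. If ward rates differ appreciably and the margin above 80% is thin, the trial could miss a true 40% reduction more often than stated. A null result on this co-primary outcome would then be easier to misread as evidence of no effect.

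**Working it through.** **Inputs.** From the Sample size section: control mean m0 = 5.22, intervention mean m1 = 3.13, n = 16 wards per arm (17 if none drops out), beds 18-30 with mean 24. Assumed: two-sided 5% (the section gives 5% only for the WEMWBS calculation), and the between-ward CV, for which the document gives no value.

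**Step 1: reproduce the stated figure (CV = 0, one count per ward).**

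- Log rate ratio: ln(5.22/3.13) = 0.5115. SE = √[(1/5.22 + 1/3.13)/16] = √(0.5111/16) = 0.1787. z = 2.862. Power = Φ(2.862 − 1.96) = 81.6%.
- Difference: (5.22 − 3.13)/√[(5.22 + 3.13)/16] = 2.09/0.7224 = 2.893. Power = Φ(0.933) = 82.5%.
- Hayes-Bennett formula with CV = 0, for 80% power: 1 + (1.96 + 0.84)² × 8.35/2.09² = 16.0 wards per arm.

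The protocol's figure is reproduced, with about 2 to 3 points of headroom.

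**Step 2: add between-ward variation.** Take the variance of a ward's count as m + CV²m². On the log scale, SE² = (1/m0 + 1/m1 + 2CV²)/n.

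*CV at which power reaches 80%.* This needs SE = 0.5115/2.802 = 0.1826, so SE² = 0.03333.

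- 16 per arm: 16 × 0.03333 = 0.5333. CV = √[(0.5333 − 0.5111)/2] = 0.105. The difference scale gives 0.122.
- 17 per arm: 17 × 0.03333 = 0.5666. CV = √[(0.5666 − 0.5111)/2] = 0.167. The difference scale gives 0.173.

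*Bed range alone.* If beds are uniform on 18-30 and incidents are proportional to beds, CV = (12/√12)/24 = 0.144.

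**Step 3: allow for repeated counts.** If 5.22 is a mean per 3-month window and k follow-up windows are analysed with a ward effect that persists across them, replace 1/m by 1/(km). The CV² term is unchanged.

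Power (%), log scale:

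| CV | 1 count, 16/arm | 1 count, 17/arm | 2 windows, 16/arm | 3 windows, 16/arm |
|---|---|---|---|---|
| 0 | 82 | 84 | 98 | >99 |
| 0.144 (beds) | 79 | 81 | 96 | 99 |
| 0.25 | 73 | 75 | 91 | 96 |
| 0.30 | 69 | 72 | 87 | 93 |
| 0.40 | 61 | 64 | 77 | 83 |
| 0.50 | 53 | 55 | 65 | 71 |

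**Step 4: minimum detectable reduction.** Solving the Step 2 formula for m1 at 80% power, with one count per ward and 16 per arm, gives about 39% at CV 0, 45% at CV 0.30 and 52% at CV 0.50.

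**The case against.** The strongest reply is that the figure is correct on its own terms. The Poisson assumption is stated openly and the arithmetic reproduces, so this is not a calculation error. That stands.

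Second, the only variation that can be drawn from the document is the bed range. It costs about 3 points: about 79% at 16 per arm and 81% at the 17 per arm to be recruited. That stands too. The larger losses come from CVs that I have assumed. The WEMWBS ICC concerns a continuous patient score and does not tell us the CV of incident rates. Some of the spread is also handled by design, since ward gender is a fixed effect in the model and, with Trust, a minimisation factor.

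Third, three follow-up counts are collected, and a mixed model with a ward intercept suits repeated counts. If 5.22 is a 3-month mean, power is restored for CVs up to about 0.40. Adjusting for the baseline count would help further. With a fully persistent ward effect, the residual CV² is CV² × [1 − CV²/(CV² + 1/5.22)], and at CV 0.50 power becomes about 85% with two windows and 91% with three. But the Data analysis section mentions baseline covariates only for individual-level outcomes. The Sample size section gives one mean per arm and does not refer to windows. If 5.22 covers the whole follow-up, the gain from repeated windows disappears.

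A reader might also infer an inflated false-positive rate. The documents do not support that: such inflation belongs to a plain Poisson test, whereas the protocol plans a mixed model with a ward random intercept.

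**Conclusion.** The concern holds as a matter of an unsupported assumption. The stated power rests on essentially identical ward rates, which the random intercept, the bed range and the clustering allowance for the other co-primary outcome all speak against. For a single count per ward there is almost no margin: a CV just above 0.1 removes it at 16 per arm, and one of about 0.17 removes it at 17.

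A reader might go further and conclude that the trial will not have 80% power. The document does not show that. It gives neither the CV nor the time base of 5.22, and between them these move power from about 53% (CV 0.50, one count) to about 96% (CV 0.25, three windows) with 16 wards per arm. These figures rest on a two-sided 5% level, normal approximations and, for repeated windows, a ward effect that persists over time. The section should be corrected, but the point does not call the design or the number of wards into question.

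**What to change.** In the Sample size section, replace the unqualified power statement with power and minimum detectable reduction for 34 wards under an overdispersed model (negative binomial, or Poisson with a ward random effect). Show both over a stated range of CVs, for example 0.1 to 0.5, and inform the CV from Trust incident returns or blinded baseline counts. State the significance level, the time window to which 5.22 refers, and how many follow-up windows enter the primary analysis. If adjustment for the baseline count is intended for the ward-level outcome, say so and reflect it in the power.

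The cost is a rewritten paragraph and possibly a less favourable stated power. No extra wards and no change to the design or the planned model are needed.

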## Methods

### Trial design

The study is a single blind, pragmatic, cluster randomised controlled trial. The TULIPS model will be delivered at the ward level (cluster) and compared to treatment as usual within a superiority framework, using a one-to-one allocation ratio, with minimisation based on Trust and ward gender (male/female/mixed). The trial will include a 9-month internal pilot which will have clearly defined stop/go criteria. The comparator was selected on the basis of pragmatics and difficulty in identifying a suitable control comparator.

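### The per-ward recruitment target does not give the stated total: 34 wards of 11 patients is 374, not 384, and falls below the 383 the protocol requires

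*Protocol article*

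**What the plan says.** The Sample size section of the protocol article sizes the individual-level outcomes, including the co-primary WEMWBS, in a chain of steps.

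- Wards: "The recruitment target is thirty-four wards". The Trial design section adds "using a one-to-one allocation ratio", so 17 wards per arm.
- Assumptions: "We assume a between group effect size of 0.4 and an intra-cluster correlation coefficient of 0.05", and "We allow for a baseline-endpoint correlation of 0.3".
- Criterion: "We specified 85% power, 5% significance level, and calculated the average cluster size".
- Result: "The optimal design for these parameters requires 9 participants per cluster". The protocol turns this into 153 per arm and 306 in the analysis set.
- Attrition: "Accounting for attrition of 20%, by making an adjustment to this value, 383 participants are required at baseline".
- Recruitment aim: "Therefore the aim is to recruit 34 clusters with 11 participants in each cluster, giving a total sample size at baseline of 384".

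The same section expects half of a pool of 816 patients to take part, which is 408 patients.

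**The concern.** The last step presents 384 as the result of multiplying 34 by 11, and it is not. The per-ward figure implies a total below both the 384 in that sentence and the 383 required just before it.

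WEMWBS is one of two co-primary outcomes, so these numbers are what recruitment will be judged against. A trial that reached 11 patients on every ward could report that it met its per-ward target and still miss its stated total and its planned analysis set of 306. A reader cannot tell whether the planned baseline sample is 374, 383 or 384.

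**Working it through.** **Inputs** (Sample size section, except the 1:1 ratio, which is in Trial design): 34 wards, 17 per arm; standardised effect 0.4; ICC 0.05; baseline-endpoint correlation 0.3; 85% power; 5% significance level, taken as two-sided because the text does not say; 9 analysed per ward; 20% attrition; 11 recruited per ward.

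**Step 1. Reproduce the 9 per ward.** For m analysed patients per ward, the variance of the standardised difference is

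Var = 2 × (1 − 0.3²) × (1 + (m − 1) × 0.05) / (17 × m).

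For m = 9: 2 × 0.91 × 1.40 / 153 = 0.01665, so SE = 0.1290 and 0.4/SE = 3.10. The normal approximation gives 87.3% power; the t version with 32 degrees of freedom gives 85.2%.

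For m = 8: 2 × 0.91 × 1.35 / 136 = 0.01807, so SE = 0.1344 and 0.4/SE = 2.98. Power is 84.5% (normal) or 82.3% (t).

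Nine is therefore the smallest whole number that reaches 85% under either version, and the protocol's figure reproduces.

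**Step 2. Reproduce the analysis set and the inflation.** 17 × 9 = 153 per arm and 34 × 9 = 306 in total. Then 306/0.8 = 382.5, rounded up to 383. Both figures reproduce.

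**Step 3. Check the recruitment aim.** 34 × 11 = 374.

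- Against the stated total: 384 − 374 = 10 short.
- Against the stated requirement: 383 − 374 = 9 short.
- Average needed for 383: 383/34 = 11.26 per ward. For 384: 384/34 = 11.29.

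This is the only step that does not reproduce.

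**Step 4. Where 384 probably comes from.** Applying attrition to each arm and rounding up gives 153/0.8 = 191.25, so 192 per arm and 2 × 192 = 384. On that reading 384 is a valid total, and 11 is 11.29 rounded down. This is an inference; the protocol does not show the step.

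**Step 5. Consequence if 11 per ward is what is recruited.** 374 × 0.8 = 299.2 analysed, and 299.2/34 = 8.8 per ward. For m = 8.8: 2 × 0.91 × 1.39 / 149.6 = 0.01691, so SE = 0.1300 and 0.4/SE = 3.08.

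| Analysed per ward | Power, normal | Power, t (32 df) |
|---|---|---|
| 9 (306 in total) | 87.3% | 85.2% |
| 8.8 (299 in total) | 86.8% | 84.7% |

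The loss is about 0.5 percentage points under either version.

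**The case against.** The strongest reply is that this is a rounding slip with almost no consequence. The total of 384 is adequate and has a natural origin in per-arm rounding. The calculation is described as one for the average cluster size, so 11 may be a rounded average. Nothing makes 11 a quota or a stopping point: the Recruitment section says that every eligible patient on the ward will be approached. The expected uptake of 408 is 12 per ward, which after 20% attrition leaves about 326 (408 × 0.8 = 326.4, or 9.6 per ward), above the 306 needed. Under the normal approximation even 8.8 per ward exceeds 85% power, and the protocol does not say which version was used. Finally, a further 9 patients per ward complete the WEMWBS at 6 months, with the stated purpose of securing power for that outcome.

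Much of this stands as a limit on the consequence. The shortfall arises only if wards recruit 11 and no more, and a breach of the 85% criterion is not established. It does not remove the contradiction. The sentence specifies 11 in each ward, with no mention of an average, and gives 384 as the product. Rounding a required minimum down is itself what creates the gap. The expected 408 is a forecast of uptake, not the target. The additional 6-month patients are recruited separately and have no follow-up, and the article does not say that they replace losses from the baseline cohort.

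**Conclusion.** The concern holds. The recruitment aim is wrong as written: 34 wards of 11 patients is 374, which is 10 below the stated total and 9 below the stated requirement. This part needs no assumption, and nothing elsewhere in the article reconciles the figures.

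The effect on power is minor: about half a percentage point, with 299 analysed in place of 306. That estimate assumes exactly 11 recruited on every ward, the protocol's 20% attrition spread evenly, equal ward sizes, a two-sided 5% test and the protocol's own effect size, ICC and correlation. It should not be read as showing that the trial is materially underpowered. The reason to correct it is that the target for a co-primary outcome is given in two incompatible forms. The more likely fault is in the per-ward figure, not the total.

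**What to change.** Make the total the governing target and express the ward figure as an average: at least 383 patients at baseline across 34 wards, about 11.3 per ward. As one illustration, 24 wards of 11 and 10 wards of 12 give 264 + 120 = 384; no particular split is needed. A uniform whole number of 12 per ward would also satisfy the requirement, but 34 × 12 = 408 is the entire expected uptake and leaves no margin.

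If 11 per ward is really intended, restate the plan as 374 recruited and about 299 analysed, and give the resulting power and the method used to compute it.

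The first option costs one corrected sentence and at most about 10 more patients than 11 per ward would yield, within the 408 already expected. Design and analysis are unchanged.

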During the ward recruitment period, all staff on the ward and all patients on the ward meeting inclusion criteria will be approached about the study. Researchers will base themselves on the wards during the recruitment periods in order to promote the study and maximise opportunities for recruitment. Staff and patients will be provided with a written copy of the participant information sheet describing the details of the study. Where possible, potential participants will be given at least 24 hours to decide whether or not they would like to participate. However, if a participant wants to take part before this 24-hour window, we will give them the opportunity to do so. In all instances, participants will be provided with the opportunity to read the participant information sheet, be provided with the opportunity to ask questions about the research, and have their questions answered satisfactorily. They will be asked to consent to completing self-reported outcome measures and/or consent to take part in a qualitative interview. The information sheet and consent form will state that their participation is entirely voluntary and that they are free to withdraw from the study at any point. It is likely that most of the patients recruited at baseline will be discharged before the follow-up period. Therefore, follow-up measures will be completed in community settings. Researchers will take a proactive approach to follow-up assessment which will involve multiple attempts to contact people and being flexible with appointment times and locations, including the possibility of conducting follow-ups via email/ Microsoft Teams (staff) and/or phone (staff and patients).

Separate consent will be sought from patients on the ward at 6-month follow-up to complete the Views on Inpatient Care (VOICE; [20]). This is because it is likely different patients who will need to be recruited from baseline given the probability that the same patients will no longer be on the ward. Although participants will not be blind to the treatment condition of the ward, there will be a separate participant information sheet for the VOICE, which will not explicitly refer to the fact that the study is testing the effects of providing psychological therapies on inpatient wards. Potential participants will be informed that the study is assessing patient satisfaction with wards with different compositions of multidisciplinary team members**.**

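### New inpatients recruited at 6 months are given the job of powering the WEMWBS co-primary, although they have no baseline, are recruited once the ward's condition is known, and are sized by a baseline-adjusted design

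*Protocol article*

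**What the plan says.** All section names refer to the protocol article.

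- **Sample size**, on the 6-month VOICE recruits: "At the 6-month follow-up where additional patients will be recruited to complete the VOICE they will also complete the primary outcome measure (WEMWBS"). The next sentence says this is done so that the primary outcome has enough power. Their number follows: "9 patients per cluster will be recruited, as per the aforementioned optimal design for the defined power and significance level parameters". The only stated change from the cohort calculation is that no drop-out allowance is needed.
- **Sample size**, on the design being reused: "We assume a between group effect size of 0.4 and an intra-cluster correlation coefficient of 0.05"; "We allow for a baseline-endpoint correlation of 0.3"; "We specified 85% power, 5% significance level". It arrives at 9 per ward, 153 per arm, 306 analysed and 383 at baseline after 20% attrition.
- **Table 1** has a single WEMWBS row. Its 6-month cell covers the cohort and the VOICE participants together. VOICE participants have no baseline or 9-month entry.
- **Recruitment** expects most baseline patients to have been discharged by follow-up and assessed in the community. It expects the VOICE sample to be largely different people, and says of them: "Although participants will not be blind to the treatment condition of the ward". Their separate information sheet does not disclose that psychological therapy provision is being tested.
- **Blinding and Randomisation** conceals ward allocation from potential participants until their baseline measures are done, as a guard against selection bias.
- **Data analysis**: "With the exception of patient ward atmosphere (VOICE), the baseline values of the outcomes can be used as a covariate in the models".

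**The concern.** A sample can help to power an outcome only if its data count toward that outcome. The stated purpose and the shared Table 1 row therefore both point to the VOICE recruits' WEMWBS contributing to a co-primary. Four features make that unsafe.

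1. **Different population.** The cohort is mostly discharged patients. The VOICE sample is whoever is an inpatient six months into the intervention.
2. **Possible selection by treatment.** The Outcome measures section expects better symptoms and functioning to shorten admissions. On that reasoning the intervention can change who is on the ward at 6 months.
3. **No concealment at recruitment.** The cohort is approached with allocation concealed from potential participants. The VOICE recruits are approached on wards whose condition is known, and the separate information sheet masks the purpose only in part.
4. **No baseline score.** The baseline adjustment offered for the WEMWBS, and used in its power calculation, is not available for these patients in its ordinary form.

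At stake is whether a difference in a co-primary reflects the treatment or reflects who was admitted and agreed to take part. A second, smaller matter is that the size of this sample was justified by a calculation that does not apply to it.

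**Working it through.** **Inputs (Sample size section unless noted).** Effect d = 0.4; ICC ρ = 0.05; baseline-endpoint correlation r = 0.3; 85% power; 5% significance, taken as two-sided because sidedness is not stated. "The recruitment target is thirty-four wards", and allocation is one-to-one (Trial design), so k = 17 wards per arm.

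**Step 1. Reproduce the stated 9 per ward.**
- Individually randomised n per arm = 2(1.960 + 1.036)² / 0.4² = 112.2.
- Baseline adjustment: 112.2 × (1 − 0.3²) = 112.2 × 0.91 = 102.1.
- Cluster size m = n(1 − ρ) / (k − nρ) = 102.1 × 0.95 / (17 − 5.11) = 8.16, rounded up to 9.
- 17 × 9 = 153; 34 × 9 = 306; 306 / 0.8 = 382.5, so 383. All four stated figures reproduce.

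Power at 9 per ward, with variance 2(1 − r²)[1 + (m − 1)ρ] / (km):
- Variance = 2 × 0.91 × 1.40 / 153 = 0.01665, SE 0.1290, and 0.4 / 0.1290 = 3.100.
- Power is 87.3% (normal) or 85.2% (t, 32 df).

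**Step 2. Remove the baseline, as the VOICE recruits require (r = 0).**
- m = 112.2 × 0.95 / (17 − 5.61) = 9.36, so 10 per ward by the normal approximation.
- At 9 per ward: variance = 2 × 1.40 / 153 = 0.01830, SE 0.1353, ratio 2.957.

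| Per ward, r = 0 | Normal | t, 32 df |
|---|---|---|
| 9 | 84.1% | 81.8% |
| 10 | 86.5% | 84.4% |
| 11 | 88.5% | 86.5% |

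The specified 85% needs 10 per ward (normal) or 11 (t). Over an assumed ICC range of 0.01 to 0.10, normal-approximation power at 9 per ward without a baseline runs from 92.0% to 74.1%.

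**Step 3. Illustrate the bias if the samples were pooled.** Assumptions, none taken from the documents: 9 cohort and 9 VOICE patients per ward, equal weight, no baseline adjustment, no term for sample, and a between-arm selection difference s in the VOICE half only.
- SE = √(2 × [1 + 17 × 0.05] / (17 × 18)) = √(2 × 1.85 / 306) = 0.110.
- Bias in the pooled estimate = s / 2.

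| s (SD) | Bias (SD) | Bias / SE | Type I error |
|---|---|---|---|
| 0.1 | 0.05 | 0.45 | 7.4% |
| 0.2 | 0.10 | 0.91 | 14.9% |
| 0.3 | 0.15 | 1.36 | 27.6% |

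**Step 4. What the cohort supplies alone.** The section's recruitment aim is 11 per ward: 34 × 11 = 374, although the text gives 384. After 20% attrition, 374 × 0.8 = 299, or 8.8 per ward. With r = 0.3 that gives 86.8% (normal) or 84.7% (t). With 16 wards per arm, the number used to power the incident outcome, it gives 84.7% (normal) or 82.3% (t, 30 df).

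**The case against.** **Pooling is not written down.** A reader might infer that the protocol commits to one model containing both samples. It does not. A full 9 per ward with no drop-out allowance also fits a free-standing 6-month cross-section, and the detailed model may be left to the analysis plan. This stands, so the bias is conditional. What remains is that the protocol itself assigns these data to powering the primary outcome, and that assignment is the statement to correct.

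**The type I figures are illustrative.** The selection differences are assumed, and the table holds only for equal, unadjusted pooling. This stands; the figures show scale and predict nothing.

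**The cohort is also recruited after randomisation and unblinded later.** True, according to Recruitment and to Blinding and Randomisation, and WEMWBS assessors are blind for everyone. The contrast is narrower: concealment from participants at the time of recruitment.

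**A missing baseline need not exclude anyone.** The text says baseline values can be used, and models that treat baseline as an outcome keep patients without one. It would be too strong to say that these patients must be dropped or the covariate abandoned. Such models do not remove selection.

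**Exposed inpatients are a legitimate target.** The intervention covers everyone on the ward, and some cohort members may receive little of it before discharge. That supports reporting this comparison separately; it does not support merging it with the cohort.

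**A reserve has some rationale.** A reader might conclude that the extra sample is superfluous because the cohort alone delivers 306. At 11 per ward it delivers about 299, so that conclusion fails.

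**Double counting of readmitted patients** might also be feared, but the text calls the recruits additional patients and gives no ground for assuming overlap.

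**Conclusion.** The point holds in a conditional form for the bias and outright for the sample size. The protocol gives a co-primary powering role to patients who are probably not the cohort, are recruited with the ward's condition known, may be selected through length of stay, and have no baseline. If their scores count toward the co-primary, the estimate is open to selection bias whose size the documents do not allow anyone to estimate. Type I error of about 7% to 28% follows only under the stated assumptions.

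The reuse of 9 per ward is a definite but small error: 84.1% (normal) or 81.8% (t) in place of 85%, given d = 0.4, ICC 0.05 and 17 wards per arm. The weight of the point lies in the undefined co-primary population, not in this shortfall of about 1 to 3 percentage points.

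**What to change.** 1. Define the WEMWBS co-primary on the baseline cohort, adjusted for baseline WEMWBS.
2. Report the VOICE participants' WEMWBS as a separate, secondary, cross-sectional comparison at 6 months, and show this separation in Table 1.
3. Delete the sentence saying that these participants ensure power for the primary outcome.
4. Restate the power of the 9-per-ward sample as about 82–84%, without baseline adjustment.
5. State what the cohort alone provides: at 11 recruited per ward, about 299 analysed rather than 306, with about 87% power (normal) or just under 85% (t).

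The change is to wording only, and all planned data are still collected. The cost is that the co-primary gains no precision from the VOICE sample, and by the t calculation the cohort falls marginally short of 85% at 11 per ward.
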